# Efficacy of laparoscopic subtotal gastrectomy with D2 lymphadenectomy for locally advanced gastric cancer: the protocol of the KLASS-02 multicenter randomized controlled clinical trial

**DOI:** 10.1186/s12885-015-1365-z

**Published:** 2015-05-05

**Keywords:** Gastric neoplasm, Laparoscopy, D2 lymphadenectomy, Advanced gastric cancer

## Abstract

**Background:**

Despite the well-described benefits of laparoscopic surgery such as lower operative blood loss and enhanced postoperative recovery in gastric cancer surgery, the application of laparoscopic surgery in patients with locally advanced gastric cancer (AGC) remains elusive owing to a lack of clinical evidence. Recently, the Korean Laparoscopic Surgical Society Group launched a new multicenter randomized clinical trial (RCT) to compare laparoscopic and open D2 lymphadenectomy for patients with locally AGC. Here, we introduce the protocol of this clinical trial.

**Methods/design:**

This trial is an investigator-initiated, randomized, controlled, parallel group, non-inferiority trial. Gastric cancer patients diagnosed with primary tumors that have invaded into the muscle propria and not into an adjacent organ (cT2–cT4a) in preoperative studies are recruited. Another criterion for recruitment is no lymph node metastasis or limited perigastric lymph node (including lymph nodes around the left gastric artery) metastasis. A total 1,050 patients in both groups are required to statistically show non-inferiority of the laparoscopic approach with respect to the primary end-point, relapse-free survival of 3 years. Secondary outcomes include postoperative morbidity and mortality, postoperative recovery, quality of life, and overall survival. Surgeons who are validated through peer-review of their surgery videos can participate in this clinical trial.

**Discussion:**

This clinical trial was designed to maintain the principles of a surgical clinical trial with internal validity for participating surgeons. Through the KLASS-02 RCT, we hope to show the efficacy of laparoscopic D2 lymphadenectomy in AGC patients compared with the open procedure.

**Trial registration:**

ClinicalTrial.gov, NCT01456598.

## Background

Since the first laparoscopic gastrectomy for gastric cancer was performed in 1994 [1], increasingly more surgeons have performed this procedure in East Asian countries such as Korea and Japan [2]. Nevertheless, the Japanese Gastric Cancer Association (JGCA) treatment guideline recommends that laparoscopic surgery for gastric cancer should not be performed as a general practice [3]. The reason for this recommendation is that despite the benefits of laparoscopic surgery, the long-term survival results from 2 multicenter randomized clinical trials (RCTs) in Japan (registered in the University Hospital Medical Information Network [UMIN] Clinical Trial Registry as UMIN000003319) and Korea (registered in the National Institutes of Health [NIH] Clinical Trail Registry as NCT0045251) have not been reported. However, the interim analysis of a multicenter RCT conducted by Korean surgeons described the safety of laparoscopic surgery for early gastric cancer (EGC) [4]. In addition, several meta-analyses have showed that laparoscopic gastrectomy with limited lymphadenectomy for patients with EGC had non-inferior oncologic outcome relative to open surgery, and a benefit in terms of faster postoperative recovery [5-7]. Based on this evidence, most experienced surgeons have applied the laparoscopic procedure in patients with EGC.

However, the use of laparoscopic surgery in patients with locally advanced gastric cancer (AGC) remains controversial. Several obstacles have been considered as the reasons for this limitation. First, extended (D2) lymphadenectomy is an essential procedure for performing curative resection in AGC patients, which requires more sophisticated surgical techniques to ensure patient safety. Owing to some limitations of laparoscopic surgery such as impossible palpation, unsecure bleeding control, among others, the experience and skill of surgeons is more important in laparoscopic surgery for AGC. Second, some researchers have expressed the concern that the laparoscopic procedure for advanced malignant disease might aggravate cancer progression via the intraoperative intraperitoneal pressure and circulating gas. However, there is no conclusive evidence to support this hypothesis to date. Taken together, the application of laparoscopic surgery in patients with locally AGC is possible if the technical and oncologic safety is ensured.

A well-designed multicenter RCT recruiting a large sample of patients is the best option to obtain clinical evidence for novel technology in the surgical field. Considering the benefits of laparoscopic surgery, such as enhanced postoperative recovery and reduced postoperative pain, the application of laparoscopic surgery will likely be extended to more patients with AGC and EGC. Currently, the Korean Laparoscopic Surgical Society (KLASS) group launched the multicenter RCT (KLASS-02 RCT; registered at www.clinicaltrials.gov as NCT01456598) to compare the oncologic and surgical outcomes between laparoscopic and open extended lymphadenectomy in patients with locally AGC. In particular, since extended lymphadenectomy in gastric cancer surgery has been regarded as a convoluted procedure, the internal validity for the surgical technique of surgeons participating in this RCT is deemed a crucial prerequisite for this surgical RCT. Therefore, the KLASS-02-QC (registered at www.clinicaltrials.gov as NCT01283893), a study conducted to standardize the procedures of laparoscopic and open extended D2 lymphadenectomy, will be performed separately [8]. Surgeons validated through the strict qualification program of the KLASS-02-QC RCT can participate. In addition, this RCT is elaborately designed to minimize the sources of bias and distortion of the results, which can be exaggerated in a surgical clinical trial. Here, we introduce the protocol of the KLASS-02 RCT comparing laparoscopic and open D2 lymphadenectomy for patients with locally AGC.

## Methods

### Objectives

The purpose of the KLASS-02 RCT is to show the efficacy of laparoscopic distal gastrectomy with extended D2 lymphadenectomy for patients who are clinically diagnosed with locally AGC, compared with conventional open subtotal gastrectomy and D2 lymphadenectomy.

### Study design

This RCT is an investigator-initiated, randomized, controlled, parallel group, and non-inferiority trial comparing laparoscopic D2 lymphadenectomy for locally AGC patients with open conventional surgery.

Before enrollment of first patient, this study was approved from the institutional review boards (AJIRB-MED-MDB-11-223) of Ajou university hospital, Soonchunhyang university hospital, Keimyung university hospital, Chonnam national university hwasun hospital, Incheon St. Mary’s hospital, Yeoeuido St. Mary’s hospital, Dong-A university hospital, Seoul national university hospital, Seoul national university bundang hospital, Yonsei university severance hospital, Yonsei university gangnam severance hospital, Ewha womans university hospital and National cancer center. All investigators progress this study in accordance with the Declaration of Helsinki [9]. An independent institutional review board of all institutions at which the participating surgeons are affiliated has approved this study. Written informed consent will be obtained from all patients before they are recruited. This RCT will be monitored by an independent data and safety monitoring committee (DSMC) organized by the Clinical Trial Center of Ajou University Hospital.

### Study population

The patient inclusion and exclusion criteria are as follows:

#### Inclusion criteria

Patients aged >20 and <80 yearsPatients with an Eastern Cooperative Oncology Group (ECOG) performance status of 0 or 1Patients with American Society of Anesthesiology score of class I to IIIPatients diagnosed with gastric adenocarcinoma that is possible to be curatively resected by subtotal gastrectomyPatients with primary gastric carcinoma that has invaded into the muscle propria, not into an adjacent organ (cT2 to cT4a) in preoperative studiesPatients with no lymph node metastasis or limited perigastric lymph node metastasis (including lymph nodes around the left gastric artery) in preoperative studiesPatients who agree to participate in the clinical study through informed consent.

#### Exclusion criteria

Patients with possible distant metastasis in preoperative studiesPatients who underwent past gastric resectionPatients with gastric cancer-related complications (complete obstruction or perforation)Patients treated by chemotherapy or radiotherapy for gastric cancerPatients diagnosed with other malignancy within 5 yearsVulnerable patientsPatients who are participating or have participated in another clinical trial within the past 6 months.

### Study protocol

The Ajou ARO (Academic Research Organization) in Ajou University Hospital will manage this clinical trial. As soon as the participating surgeons obtain informed consent from the patients, researchers entered the patient information into an web-based electrical clinical report form (eCRF;http://clintrial.ajoumc.or.kr/klass02/). The beta version of eCRF system tested at each actual site before full implementation, to ensure data capture system and to reduce user error. The eCRF system is automatically given screening number according to the sequence in which the informed consent forms are received. And if patients meet the criteria for a randomization, then eCRF system assigned at each surgery group.. Finally, the system provides an allocation number with a pre-generated randomized code for those who are selected by inclusion and exclusion criteria. A randomized block design is applied for randomization with each investigator as the stratification factor (R 2.10.1). To maintain the properties of randomization, block size is not open to the investigators. The surgeons are immediately notified of the randomization results via e-mail. After notification, the surgeons let the patients know which type of operation they will undergo. Therefore, the surgeon and patient blinding is impossible owing to the nature of surgical RCT. However, the protocol recommends that ward staff members evaluating patient outcomes be blinded, if possible. If the surgeon does not perform the operation within 30 days after recruitment, the patients are excluded from the trial. These patients will need to be re-evaluated for re-recruitment into this RCT.

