#### Postoperative care

The ward staff will evaluate the patients every morning and afternoon for the presence of any issues affecting the patients’ recovery. The degree of pain, diet schedule, and gas out were daily recorded until discharged, and laboratory findings are recorded on the first and fifth postoperative day. After surgery, the surgeon can progress the diet schedule from sips of water to a soft diet according to the patient’s condition. If the patients are in good condition 2 or 3 days after starting a soft diet and do not have complaints regarding their status, they can be discharged from the hospital.

After fully recovering from surgery, patients diagnosed with Stage II (except T1) or Stage III cancer in the final pathology report will be recommended for adjuvant chemotherapy based on 5-fluorouracil administration. Adjuvant chemotherapy will be started from 4–6 weeks postoperatively, if the patients’ general condition is suitable for chemotherapy.

After curative resection, all patients will be regularly evaluated for disease recurrence postoperatively every 3 or 6 months over a 3-year period. Abdominopelvic computed tomography (CT), serum tumor markers (CEA and CA19-9), and other parameters can be included in studies for regular follow-up.

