### Outcome measurements

The primary endpoint of the KLASS-02 RCT is non-inferiority in the 3-year relapse-free survival rate after laparoscopic subtotal gastrectomy and extended lymphadenectomy for locally AGC compared with open conventional surgery. To measure this endpoint, the criteria for recurrence are suggested in detail. Recurrence can be detected on regular follow-up studies such as abdominopelvic CT in patients without specific symptoms through a formal radiology report. If the results of follow-up studies are suspicious, whole-body positron emission tomography-CT, magnetic resonance imaging of the liver, or laparoscopic exploration can be performed to confirm recurrence. Otherwise, patients can attend follow-ups at shorter intervals than the planned schedule. Patients with specific symptoms, such as abdominal mass, weight loss, or intestinal obstruction, which might coincide with recurrence, should be evaluated for recurrence immediately regardless of the follow-up schedule. Surgeon should report recurrence in enrolled patients by entering this information into the eCRF as soon as the recurrence is confirmed.

Secondary outcomes include postoperative morbidity and mortality, postoperative recovery, and quality of life. Complications are divided into early and late morbidities depending on time of occurrence. Early morbidity is defined as surgery-related complications occurring within 21 days postoperatively, and includes the events listed in Table 2. Complication severity is classified according to grading system suggested by Dindo D et al. [10]. Regarding postoperative morbidity, the operative time and blood loss volume are also recorded. In cases of conversion from laparoscopic to open surgery, the reason for conversion should be explained. The events related to late morbidity, which occur after the 28th postoperative day, are listed in Table 2.

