## Discussion

To the best of our knowledge, this study is the first multicenter randomized clinical trial recruiting a large number of patients to compare laparoscopic D2 lymphadenectomy with open conventional lymphadenectomy in patients preoperatively diagnosed with locally AGC. Through this clinical trial, we aim to show the non-inferiority in the 3-year relapse-free survival rate of patients undergoing laparoscopic procedures compared with open surgery as the primary end point. In addition, laparoscopic surgery is expected to show comparable surgical outcomes such as morbidity and mortality, and improved postoperative recovery. Particularly, we sought to design the trial to overcome the challenges confronting surgical clinical trials while following the general principles of multicenter RCTs.

In general, multicenter RCTs should be designed according to specific principles such as evidence-based calculation of sample size, concealment of randomization, interim analysis, ITT analysis, and blinding to the type of intervention to avoid bias. Our protocol was established by following these general principles as closely as possible. However, blinding of the surgeons and patients to the intervention is impossible in most surgical clinical trials. In particular, when comparing laparoscopic surgery with conventional laparotomy as in the present RCT, blinding between 2 surgical procedures cannot be achieved due to the technical difficulty. In some previous surgical RCTs, postoperative dressings were applied using the same methods for patients who underwent both laparoscopic and open cholecystectomy, thus the type of intervention was blinded to patients and ward staff [14,15]. However, it is unlikely that perfect blinding using the same dressing is achieved, and blinding patients to the type of surgery might cause ethical issues. Non-blinding of staff investigating the outcomes will likely cause subjective measurement of them. To minimize the bias due to non-blinded randomization in the present RCT, we suggested the objective outcomes as endpoints. Therefore, the criteria for recurrence, the primary endpoint of this RCT, were described in detail.

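### Masking is recommended only for ward staff who follow in-hospital recovery; the radiology report that detects recurrence may be made with the arm known

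*Protocol article*

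**What the plan says.** On blinding, the Study protocol section of the Protocol article states: "Therefore, the surgeon and patient blinding is impossible owing to the nature of surgical RCT". It then gives the one masking measure in the document: "However, the protocol recommends that ward staff members evaluating patient outcomes be blinded, if possible". Postoperative care describes what those staff do: "The ward staff will evaluate the patients every morning and afternoon for the presence of any issues affecting the patients’ recovery".

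Outcome measurements sets the primary endpoint: "The primary endpoint of the KLASS-02 RCT is non-inferiority in the 3-year relapse-free survival rate". Recurrence can be found on regular follow-up studies such as abdominopelvic CT "in patients without specific symptoms through a formal radiology report". A middle category follows: "If the results of follow-up studies are suspicious", PET-CT, "magnetic resonance imaging of the liver, or laparoscopic exploration can be performed to confirm recurrence", or the patient may be seen again sooner. Patients with symptoms are evaluated at once. The surgeon enters confirmed recurrence in the eCRF.

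The Discussion takes up assessor bias directly: "Non-blinding of staff investigating the outcomes will likely cause subjective measurement of them". Its answer is that the endpoints were chosen to be objective and that the recurrence criteria are set out in detail. It mentions no masked reading of imaging.

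**The concern.** The one masking measure is aimed at secondary, in-hospital outcomes. The primary endpoint is left to the objectivity of recurrence. That defence is incomplete, because the criteria name the tests and the type of report but give no imaging threshold for calling recurrence, and they contain a suspicious category. Deciding whether a scan is negative, suspicious or recurrent is a judgement, and the Discussion itself says that unmasked judgement tends to be subjective.

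The stake is specific to non-inferiority. If equivocal scans were read more leniently after laparoscopy, fewer laparoscopic events would be counted, the observed hazard ratio would fall, and a truly inferior procedure could pass the margin more often than the nominal error rate allows. Stricter reading after laparoscopy would do the reverse and cost power.

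The point concerns only how a scan is read. It does not concern when scans are done or how a suspicious result is worked up.

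**Working it through.** **Who is masked, and for what**

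| Role | Task | Masking described |
|---|---|---|
| Surgeon | Operates; enters recurrence in the eCRF | Impossible |
| Patient | – | Impossible |
| Ward staff | In-hospital recovery (secondary) | Recommended, if possible |
| Radiologist | Formal report that detects recurrence (primary) | Not mentioned |

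**Inputs from Sample size calculation.** Margin hazard ratio (HR) 1.43; 90% power; 330 events; 525 patients per group (1:1). The type I error is printed as 0.25 one-sided.

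**Reproducing the plan's figure.** Schoenfeld's formula for 1:1 allocation and a true HR of 1 is events = 4(z_alpha + z_beta)² / (ln 1.43)².
- One-sided 0.025: 4(1.960 + 1.282)² / (0.3577)² = 328.5, so 329, against the stated 330.
- One-sided 0.25: 120.

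The event count fits 0.025, so I use 0.025. The printed 0.25 is a separate matter.

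**Precision.** SE(ln HR) = 2/√330 = 0.110. Non-inferiority is shown if the observed HR is below 1.43 / exp(1.96 × 0.110) = 1.15.

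**Upper bound: relapses never called.** Let f be the fraction of laparoscopic relapses never called, with none missed in the open arm. The document gives no value for f; those below are assumptions. With a true HR at the margin:
- Observed HR ≈ 1.43 × (1 − f)
- P(false non-inferiority) = Φ(−1.96 − ln(1 − f)/0.110)

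| f | Observed HR | −ln(1 − f)/0.110 | False non-inferiority |
|---|---|---|---|
| 0 | 1.43 | 0 | 2.5% |
| 2% | 1.40 | 0.18 | 3.8% |
| 3% | 1.39 | 0.28 | 4.6% |
| 5% | 1.36 | 0.47 | 6.8% |
| 10% | 1.29 | 0.96 | 15.8% |

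**Milder case: relapses called late.** Patients are re-evaluated every 3 or 6 months for 3 years, so a relapse read leniently once would usually be called at a later visit. I simulated this with hazards of 0.11 and 0.11 × 1.43 = 0.157 per year, 3 years of follow-up, 330 events, one-sided 0.025, and a fraction of laparoscopic relapses called 6 months late.

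| Fraction called 6 months late | Observed HR | False non-inferiority |
|---|---|---|
| 5% | about 1.41 | about 3.3% |
| 10% | about 1.40 | about 3.7% |

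A repeat run agreed to about 0.1 percentage points. The effect is small because most late calls still fall within 3 years. The share of laparoscopic relapses arising in the last 6 months is (exp(−0.157 × 2.5) − exp(−0.157 × 3)) / (1 − exp(−0.157 × 3)), about 14%. Only that share of the delayed relapses drops out of the 3-year window.

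**The case against.** Five points can fairly be made on the other side.

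1. **A reader might infer that the primary endpoint is in fact read with the arm known.** The article does not say so. It is silent on what the radiologist is told, and the full protocol, which is not shown, may specify it. This stands, and the point is limited to *may be read*. It is still more than an omission through brevity, because the article says who should be masked and gives its own argument for why recurrence is protected. That argument can be tested on its own terms.

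2. **The article has a strategy.** It names objective endpoints, a formal report, and further tests for suspicious findings. This stands in part. Clear-cut or symptomatic relapses are little exposed to reader judgement. The suspicious category is exposed, and the further tests are optional.

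3. **A reader might infer that the bias favours laparoscopy.** Nothing in the document shows that radiologists lean that way. The Background reports a concern that laparoscopy could aggravate progression, and a reader who shared it might over-call. This stands: the direction is unknown.

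4. **A reader might take 15.8% as the expected size.** It is not. It treats under-called relapses as lost for good and applies the fraction to all laparoscopic relapses, although only equivocal scans are at issue. This stands, so the figure is an upper-bound illustration.

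5. **Masking the radiologist leaves the surgeon unmasked**, and the surgeon enters the event. This stands as a limit on what the fix achieves. It is no reason to leave the reading open.

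**Conclusion.** The concern holds in a limited form. The described masking reaches in-hospital recovery and stops short of the primary endpoint. The stated reliance on objectivity does not cover scans that need judgement. The radiology report may be made with the arm known, and differential reading in either direction is not guarded against.

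The documents do not support saying that readers know the arm, that they favour laparoscopy, or that the error rate is inflated by any particular amount. If lenient reading after laparoscopy did occur, the false non-inferiority rate would lie between a small rise when relapses are called late (about 3.3% to 3.7% for 5% to 10% delayed by 6 months) and the upper bound when they are never called (6.8% to 15.8% for the same fractions), against 2.5%. These figures assume a true HR of 1.43, one-sided 0.025, 330 events and the illustrative fractions. This is a worthwhile low-cost improvement, not a flaw that invalidates the design.

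**What to change.** Extend the masking recommendation in the Study protocol section to the primary endpoint:
- Requests for follow-up imaging, including any PET-CT or MRI, state the resection and reconstruction but not whether the approach was laparoscopic or open.
- The routine radiologist issues the formal report without being told the arm.
- The eCRF records whether the reader was masked.

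The timing of scans and the handling of suspicious results stay as they are. No second reader or central review is required.

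The cost is one protocol sentence, a change to the imaging request text and one eCRF field. If sites already read this way, the sentence simply documents it. The downside is that masking will be imperfect: scars may be visible and hospital records can be opened. It also does not mask the surgeon who enters the recurrence. It therefore reduces the bias without removing it, and the eCRF field would show how often masking was achieved.

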### Patient groups for statistical analysis

The efficacy for the primary and secondary outcomes will be evaluated in different groups of patients according to the surgical results. Except for the patients who are not undergoing surgery or have unresectable tumors, all patients will be included in the intention-to-treat (IIT) group. The postoperative recovery, morbidity and mortality, quality of life, and overall survival will be evaluated for the patients in IIT group. The 3-year relapse-free survival will be analyzed for patients in the full analysis set (FAS) group. ITT group patients who cannot undergo curative resection and have synchronous tumors or distant metastases un-defined at the screening step, will be additionally excluded from the FAS group. If patients did not comply with protocol because of various reasons like as conversion of surgical type, total resection and follow up loss, then they will be excluded from the per-protocol (PP) group. When the difference between the FAS and PP groups exceeds 10% of the total recruitment number, statistical analysis with the PP group patients will be performed. This RCT is schematically described in Figure 1. For safety analysis, patients in FAS group are examined with their actual treated surgery.

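### The 30-day rule removes randomised patients after their arm is known and foresees re-recruitment without keeping the first allocation, so a patient could be randomised twice

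*Protocol article*

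**What the plan says.** The Study protocol section describes the steps in order. After consent and confirmed eligibility, the eCRF allocates: "Finally, the system provides an allocation number with a pre-generated randomized code for those who are selected by inclusion and exclusion criteria". Then "The surgeons are immediately notified of the randomization results via e-mail", and "After notification, the surgeons let the patients know which type of operation they will undergo".

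The exclusion rule follows: "If the surgeon does not perform the operation within 30 days after recruitment, the patients are excluded from the trial". The next sentence deals with re-entry: "These patients will need to be re-evaluated for re-recruitment into this RCT".

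Allocation is blocked within investigator, and the one safeguard named for the sequence is that "To maintain the properties of randomization, block size is not open to the investigators".

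The section on patient groups for analysis defines the main set differently: "Except for the patients who are not undergoing surgery or have unresectable tumors, all patients will be included in the intention-to-treat (IIT) group". Surgery after day 30 is not among its reasons for leaving that set. The Discussion lists concealment and intention-to-treat analysis among the principles that the design follows as closely as it can.

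**The concern.** The exclusion acts after randomisation, in an open-label trial, on patients whose arm is known to the person who operates and to the patient. The trigger is simply that the operation was not done in time, and no reason has to be given. Delay can therefore be related to arm and to prognosis without any intent. Scheduling, hesitation over a difficult tumour, or a patient's dislike of the allocated operation would each be enough.

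If re-recruitment means passing through the same entry process, the patient receives a new allocation and may be counted in the other arm. At stake is the comparability of the arms for the primary endpoint. In a non-inferiority trial, a loss of high-risk patients from the laparoscopic arm, or their transfer to the open arm, moves the hazard ratio in the direction that favours the trial's hypothesis.

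**Working it through.** **1. Order of events.** Consent, eligibility, allocation, e-mail to the surgeon, patient informed, and only then can the 30-day limit take effect. The article does not define whether recruitment means consent or randomisation, but either start of the clock leaves time after the arm is known.

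**2. Does anything else in the article close the gap?**
- Hidden block size makes the next allocation harder to predict. It does not prevent a second draw.
- The six-month exclusion criterion concerns participation in another trial, so it does not bar re-entry into this one.
- The intention-to-treat definition leaves out patients not operated on or unresectable. For a patient operated on late, the Study protocol section says excluded, while the analysis section gives no ground for exclusion. The two are unreconciled, and no text says which allocation counts for a re-recruited patient.

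**3. What one redraw does (assumption: 1:1, before any rebalancing by blocks).** A patient whose unwanted allocation lapses ends in the wanted arm with probability 0.5 + 0.5 × 0.5 = 0.75. If a share f of unwanted allocations lapses, 1,050 × 0.5 × f patients are randomised twice and half of them change arm. For f = 1%, 5% and 10% that is about 5, 26 and 53 patients randomised twice, with about 3, 13 and 26 ending in the other arm.

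**4. Effect on the primary comparison (illustration; the article gives no rate of delay).**

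Inputs from the sample size section: 3-year relapse-free survival 72%, margin HR 1.43, 330 events, 525 patients per arm. The event number reproduces at one-sided 0.025 and 90% power: 4 × ((1.960 + 1.282)/ln 1.43)² ≈ 329. That section prints the one-sided error as 0.25, which would give about 120 events, so 0.025 is used here.

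True HR set at the margin:
- Open: risk 0.280, 525 × 0.280 = 147.0 relapses.
- Laparoscopic: risk 1 − 0.72^1.43 = 0.375, about 196.8 relapses.

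Move m patients with risk r under laparoscopy into the open arm, where their risk is r′:
- Laparoscopic risk L = (196.8 − m·r)/(525 − m)
- Open risk O = (147.0 + m·r′)/(525 + m)
- Apparent HR = ln(1 − L)/ln(1 − O)
- False non-inferiority = Φ(ln(1.43/HR) × √330/2 − 1.96)

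Applying the assumed HR to the moved patients themselves gives r′ = 1 − (1 − r)^(1/1.43). For r = 60% this is 47%.

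| Assumed scenario | Apparent HR | False non-inferiority |
|---|---|---|
| No movement | 1.43 | 2.5% |
| 10 moved, 60% risk in either arm | 1.374 | 5.5% |
| 10 moved, 60% falling to 47% | 1.388 | 4.6% |
| 5 moved, 60% falling to 47% | 1.409 | 3.4% |
| 10 moved, 45% falling to 34% | 1.416 | 3.1% |
| 10 moved, average risk (37.5% falling to 28%) | 1.430 | 2.5% |
| 10 at 60% lost from laparoscopy, none re-entering (525 open patients unchanged) | 1.409 | 3.4% |

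Worked example, second row: L = (196.8 − 6)/515 = 0.3705, O = (147 + 6)/535 = 0.2860, HR = 1.374.

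Under a 50:50 redraw, 10 patients ending in the open arm require about 20 lapsed laparoscopic allocations, which is 20/525 ≈ 4% of that arm, all in one direction.

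**The case against.** The strongest reply is that a second randomisation is inferred. The article says only that these patients are re-evaluated for re-recruitment. Whether the first allocation is kept, or the eCRF prevents a second draw, is detail that the full protocol may hold. That stands: a new allocation follows from the process described but is not stated. It does not remove the point, because the exclusion after allocation is written outright and is a weakness even if no one is drawn twice.

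A reader might also infer that allocation concealment is defeated. The article does not support this. Concealment concerns foreknowledge before assignment; the code is pre-generated, block size is undisclosed, and nothing shows that a second draw could be foreseen. Nor is it certain that the first randomisation vanishes from the analysis, since the intention-to-treat definition does not exclude patients operated on late.

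Deliberate use is also doubtful. It would mean holding a cancer patient for a month for an even chance of the other arm. Surgeons are validated for both operations, and conversion to open is allowed and recorded. An innocent purpose, rechecking eligibility when surgery is late, is plausible. All of this bears on how often the problem would occur. It does not make the exclusion independent of arm, because benign delays can differ by arm too.

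Finally, analysing already re-randomised patients by first allocation has a price: some are counted under an operation they did not receive, which can pull the hazard ratio towards 1. That is fair, and the fix allows for it.

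**Conclusion.** The point holds as a defect in a stated rule. The article removes randomised patients after their arm is known, asks for no reason, foresees their return without saying that the first allocation is kept, and does not square this with its own intention-to-treat definition or with the principle claimed in the Discussion. A patient could be randomised twice; the article does not show that any would be.

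The size is unknown because no rate of delay is given. With 5 to 10 high-risk patients (45% to 60% relapse risk) moving in one direction, false non-inferiority would be roughly 3% to 5.5% instead of 2.5%. The top of that range leaves the moved patients' 60% risk unchanged under open surgery; applying the assumed hazard ratio to them brings it to about 4.6%. If delayed patients have average prognosis, there is little or no inflation. These figures are illustrations and not forecasts.

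**What to change.** Amend the Study protocol section so that each patient is randomised once:
- A patient operated on late, or re-evaluated, keeps the original allocation number and arm and stays in the intention-to-treat set. The delay is recorded as a protocol deviation.
- The eCRF blocks a second randomisation of the same patient.
- Delays and their reasons are reported by arm.
- Any patient already re-randomised is analysed under the first allocation, with a sensitivity analysis by the operation received or without these patients, because of the possible pull towards HR 1.
- The section on patient groups for analysis is reconciled with this rule.

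The cost is a short amendment, a duplicate check in the eCRF, a table of delays and one sensitivity analysis. A few patients operated on late remain in the analysis. The 30-day limit and clinical re-evaluation before surgery are not judged and need not change for this fix.
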